### Follow-up measurements

All measurements will be repeated at four weeks and three months post-surgery. Six weeks post-surgery patients will be seen by the orthopedic surgeon for clinical and radiographic control. These are routine measurements to assess the postoperative course.

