### Analysis

The primary outcome measure will be the score on the TGUG. Secondary outcome measures will include SEMG, strength of quadriceps and gluteus medius, OHS and SF-36 questionnaire score, score on the 5tSTS, the Trendelenburg test score and the 6MWT score. Normality of data will be checked via the Kolmogorov-Smirnov test. Differences between both treatment groups at baseline and follow-up measurements will be analyzed using the chi-square statistical method for categorical variables. For continuous variables, comparisons between both groups’ baselines will be made using an independent samples t-test. Comparisons between both groups at the follow-up measurements will be made using a two-factor repeated measures Analysis of Variance (ANOVA) (group × time). Baseline values will be included as the first follow-up measurements. Differences between successive measurements within a treatment group will be analyzed using a one-factor repeated measures ANOVA. Significance value for all tests is set at *P* <0.05. The results of all subjects will be analyzed, regardless of their treatment adherence (intention-to-treat analysis).

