## Discussion

The aim of this study is to assess the difference in functional outcome after THR through the PAA, compared to THR through the AA. The main difference between these two approaches is their impact on the gluteus medius. Whereas the AA detaches two thirds of the gluteus medius, the PAA only detaches a small part of the muscle. Since the gluteus medius is one of the most important muscles for the stability of the hip joint [10–12], we hypothesize that functional outcome is better or is achieved faster if THR surgery is performed through the PAA instead of the AA.

For this study we chose to have multiple outcome measures (SEMG, strength of gluteus medius and quadriceps, the Trendelenburg test score, the 6MWD and scores on the OHS, SF-36, TGUG and 5tSTS tests) to be certain we measure all possible effects. According to Vissers *et al*. three aspects should measure functional outcome: self-perceived function, functional tests in a laboratory setting and actual daily activity [4]. Both self-perceived function (measured by the OHS and SF-36 questionnaires) and functional tests (measured by the 6MWT and the TGUG, 5tSTS and tests) are use as outcome measures in our study. However, we chose not to assess actual daily activity at this stage. Rasch *et al*. reported remaining muscle atrophy up to two years after THR [5]. Therefore, we chose to include muscle strength measurements (measured by the SEMG, MicroFET and Trendelenburg tests). If this protocol takes too much effort for our patients it is possible that we could reduce it by removing the 6MWT and the Trendelenburg test.

This study has the following limitations. First, complete blinding cannot be achieved because of the SEMG measurements of the gluteus medius and the difference in location of scar tissue for both surgical approaches. Therefore, we chose to have an independent researcher carry out SEMG measurements and note the results, ensuring the other measures will be blinded. Second, we will only evaluate the short-term outcome. Because of the difference in approach we assume that the intervention group will already show a great deal of improvement in the short-term, while the control group will improve less. In later studies it will be necessary to investigate long-term success as well.

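### The article does not fix which ANOVA term decides the primary TGUG comparison; accepting either at 0.05 would give a false-positive rate of about 9.75%, and neither term tests postoperative benefit efficiently

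*Protocol article*

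**What the plan says.** The Analysis section names one primary variable, without a time point: "The primary outcome measure will be the score on the TGUG". The Follow-up measurements section provides two postoperative assessments: "All measurements will be repeated at four weeks and three months post-surgery". The between-arm method for continuous outcomes is given in one sentence: "Comparisons between both groups at the follow-up measurements will be made using a two-factor repeated measures Analysis of Variance (ANOVA) (group × time". The next sentence settles how baseline enters: "Baseline values will be included as the first follow-up measurements". Time therefore has three levels: baseline, 4 weeks and 3 months.

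The error rule is a blanket one: "Significance value for all tests is set at" P <0.05. No overall error rate, division of alpha or order of testing is stated.

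The Discussion puts the trial hypothesis in two parts joined by *or*: "we hypothesize that functional outcome is better or is achieved faster if THR surgery is performed through the PAA instead of the AA".

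**The concern.** A two-factor repeated measures ANOVA gives two F tests that bear on treatment: the group main effect and the group × time interaction. The wording points both ways. The sentence describes a comparison of the arms at follow-up, which suggests the group effect; the label in brackets can be read either as the list of factors or as the interaction. A two-part hypothesis sits easily with two routes to success, and each route would be tested at 0.05.

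Two things are at stake. If the choice is made after both results are seen, the 5% level no longer describes the primary claim. And whichever term is chosen, it is a poor match for the question. The group effect includes a visit at which no treatment has been given. The interaction asks only whether the arms' profiles differ in any way over three visits, which can include chance imbalance at baseline or differences of opposite sign at the two follow-ups.

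**Working it through.** **Inputs from the article.** Level 0.05 per test; two arms; three time levels (Analysis and Follow-up measurements sections). The 0.05 is a set level, not a derived figure, so there is nothing to reproduce. The article gives no main-trial sample size, SD or target difference; the Power and sample size section has only a pilot of five per group. Every n above 5, and every correlation and effect size below, is therefore an assumption.

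**1. Error rate for the primary claim.**
- One pre-named term decides: 5%.
- Either term suffices, tests independent: 1 − (1 − 0.05)² = 1 − 0.9025 = 0.0975. Independence holds in a balanced design with sphericity, where the between-patient and within-patient error terms are independent.
- Upper bound when each test holds its level: 0.05 + 0.05 = 0.10.
- Simulation under no effect (100,000 trials per setting; 5, 20 and 50 per arm; three visits): 9.6–9.7% under compound symmetry. In the non-spherical settings tried it was 9.4–10.4%; there the interaction test, left uncorrected, ran at 5.6–7.7% by itself.

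**2. What each term estimates.** Let the benefit be d at both follow-ups and zero at baseline.
- Group term: (0 + d + d)/3 = 2d/3. If the benefit is present only at week 4: d/3.
- Interaction: (2 − 1) × (3 − 1) = 2 degrees of freedom, with no direction.

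**3. What this costs in power.** Assume d = 0.6 SD, 20 per arm, unit SD and equal correlation ρ = 0.5 or 0.7 between visits. For a single-contrast test, SE = √(v × 2/20), where v is the relevant variance:

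| Test | v at ρ = 0.5; 0.7 | SE | Effect/SE, sustained benefit | Effect/SE, week 4 only |
|---|---|---|---|---|
| Group term, v = (1 + 2ρ)/3 | 0.667; 0.800 | 0.258; 0.283 | 0.4/SE = 1.55; 1.41 | 0.2/SE = 0.78; 0.71 |
| Baseline-adjusted mean of both visits, v = (1 + ρ)/2 − ρ² | 0.50; 0.36 | 0.224; 0.190 | 0.6/SE = 2.68; 3.16 | 0.3/SE = 1.34; 1.58 |
| Baseline-adjusted week 4 only, v = 1 − ρ² | 0.75; 0.51 | 0.274; 0.226 | 0.6/SE = 2.19; 2.66 | 0.6/SE = 2.19; 2.66 |

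Simulated power at 0.05:
- Sustained benefit: group term about 29–33%, interaction about 47–69%, baseline-adjusted mean about 73–85%.
- Benefit at week 4 only: interaction about 48–69%, baseline-adjusted mean about a quarter to a third, baseline-adjusted week 4 difference about 56–73%.

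**4. Does the proposed sequence hold 5%?** If there is no effect at either visit, any claim requires the averaged test to reject, so the error is at most 5%. If there is an effect at one visit only, a false claim about the other requires that visit's own 0.05 test to reject, so again at most 5%.

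**The case against.** The strongest reply is that a single term already answers the whole hypothesis. Because baseline is a time level and randomised arms are expected to be equal there, any postoperative difference, lasting or early only, appears in the group × time interaction. The Discussion also expects the intervention arm to improve more in the short term than the control arm, which again suggests the interaction. On that reading the error rate is 5%. The hypothesis is a Discussion statement, not a success rule, and the full protocol or an analysis plan may name the term.

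Much of this stands. A reader might infer that the trial's real false-positive rate is 9.75%. The documents do not support that: nowhere do they say that either term is enough, and 9.75% belongs only to an either/or rule. It also stands that rejecting in the unfavourable direction is not a fault peculiar to the interaction, since any two-sided test can do so.

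A reader might also infer that the secondary outcomes make a false claim of benefit likely: sixteen measures at 0.05 would give 1 − 0.95¹⁶ = 56%. That is not supported either. The count assumes eight SF-36 scores and two electromyography measures, the formula assumes independence among plainly related measures, and the article keeps these outcomes secondary to TGUG.

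What does not fall away is that the stated model, error rule and hypothesis together leave two routes open. Even with the interaction named, the test spends two degrees of freedom and is weaker than a baseline-adjusted contrast when the benefit is sustained.

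**Conclusion.** The point holds in conditional form. The article leaves the deciding term of the primary analysis open, so the primary error rate lies between 5% (one term fixed in advance) and about 10% (either accepted), with 9.75% under independence. Separately, and whatever the decision rule, the group term shrinks a constant benefit to two thirds, and the two-degree-of-freedom interaction has less power than one baseline-adjusted contrast for a sustained benefit. The one-third loss follows from the stated handling of baseline alone. The power figures rest on the assumed 0.6 SD, 20 per arm and correlations of 0.5–0.7, and they reverse between the interaction and the averaged contrast if the benefit exists only at week 4.

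**What to change.** State one primary test: the arm difference in TGUG over the week 4 and week 12 visits, adjusted for baseline TGUG (ANCOVA on the mean of the two visits, or the equivalent contrast in a mixed model), two-sided 0.05. Test each visit at 0.05 only if this test is significant, and rest the trial's conclusion on it. Report secondary outcomes as supportive estimates with 95% confidence intervals.

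If the early effect is the main interest, name the baseline-adjusted week 4 difference as the single primary test instead. The choice between the two should follow from the clinical question and should not be left open.

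If the ANOVA must be kept, the least repair is to name one term, or to test both at 0.025 each: 1 − 0.975² = 4.94% under independence. In simulation without sphericity, and with the interaction uncorrected, that split ran at about 5.5–6.0%.

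The text change is a few sentences, but timing matters. The Trial status section says that recruitment has finished and that the trial is at statistical analysis, so the choice must be dated and made before arm results are examined; if they have already been seen, that should be declared. The price is fewer routes to a significant result and, with the averaged test, less power than the interaction for a benefit confined to week 4.

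### The repeated measures ANOVA named in the protocol analyses all subjects only if every visit is observed or imputed; a mixed model would use every observed value

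*Protocol article*

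**What the plan says.** All statements are in the protocol article.

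- **Primary outcome (Analysis):** "The primary outcome measure will be the score on the TGUG", a time in seconds and so a continuous variable.
- **Between-group test for continuous outcomes (Analysis):** "Comparisons between both groups at the follow-up measurements will be made using a two-factor repeated measures Analysis of Variance", with group and time as the two factors.
- **Baseline (Analysis):** "Baseline values will be included as the first follow-up measurements". Baseline is thus a level of the time factor, not a covariate.
- **Visits (Follow-up measurements):** "All measurements will be repeated at four weeks and three months post-surgery". With baseline this makes three time points.
- **Within-group test (Analysis):** "Differences between successive measurements within a treatment group will be analyzed using a one-factor repeated measures ANOVA".
- **Analysis set (Analysis):** "The results of all subjects will be analyzed, regardless of their treatment adherence (intention-to-treat analysis").

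Categorical variables are compared by chi-square tests, which this point does not touch. The article states no expected dropout rate.

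**The concern.** In its classical form, a repeated measures ANOVA works on a complete row of values per patient. A patient with baseline and three-month TGUG but no four-week TGUG has an incomplete row. Unless the gap is filled, the whole row goes, including the two values that were measured. The method and the analysis set named in the same section then no longer fit together, and an analysis of completers could be reported as intention-to-treat.

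Two things are at stake. The first is precision, because observed data are thrown away in a trial whose only stated size is five patients per group for the pilot. The second is validity: a complete-case comparison is generally safe only if values are missing completely at random. TGUG requires the patient to rise, walk and sit, so a patient recovering slowly at four weeks could plausibly miss it or be unable to do it. The Discussion hypothesises that recovery is better or faster in one arm, so such gaps could also differ by arm. This is reasoning about what could happen; the article reports no missing values.

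**Working it through.** The article has no dropout figure, so there is nothing of its own to reproduce. The check has three parts.

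**1. Values needed per patient.** Baseline + four weeks + three months = 3. A patient enters the classical test for an outcome only if all three are present or imputed.

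**2. Share of patients kept.** Let q be the share missing a given follow-up visit. The values of q are assumptions, and baseline is assumed complete.

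- Visits missed independently: share kept = (1 − q)².
- Same patients miss both visits: share kept = 1 − q.
- Share with at least one follow-up value when visits are missed independently: 1 − q².

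| Assumed q | ANOVA keeps, independent | ANOVA keeps, same patients | At least one follow-up value, independent |
|---|---|---|---|
| 5% | 0.95² = 90.25% | 95% | 1 − 0.0025 = 99.75% |
| 10% | 0.90² = 81% | 90% | 1 − 0.01 = 99% |
| 15% | 0.85² = 72.25% | 85% | 1 − 0.0225 = 97.75% |

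The gap between the second and fourth columns is what a method using all available visits recovers: patients with one follow-up value whom the ANOVA discards. If the same patients miss both visits, they have no follow-up value at all, and no choice of model recovers one.

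For the ten pilot patients (five per group, Power and sample size calculation), the chance that at least one is dropped is:

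- independent visits: 1 − (1 − q)²⁰ = 64%, 88% and 96% for q = 5%, 10% and 15%;
- same patients missing both: 1 − (1 − q)¹⁰ = 40%, 65% and 80%.

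**3. Behaviour of the methods.** A simulated data set of 10 patients at three time points had one value deleted, leaving 29 of 30. A standard repeated measures ANOVA routine (one within-patient factor) refused the data as unbalanced. Listwise deletion kept 9 of 10 patients. A likelihood-based mixed model kept all 10 patients and all 29 observations.

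**The case against.** The strongest reply is that the text contains no contradiction. The intention-to-treat sentence is framed by treatment adherence, and a repeated measures ANOVA excludes nobody for non-adherence or for receiving the other approach. The clash arises only if values are missing and nothing is imputed, and an article may leave imputation to the full protocol or to a statistical analysis plan that is not shown. Much of this stands. A reader might infer that the all-subjects promise is already broken; the documents do not support that, and the silence on missing data is not itself a fault. What remains is narrower: the article does fix a method, and that method meets the promise to analyse all subjects only under a condition the article does not state.

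Three further inferences should also be resisted.

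- **That the authors expect missed visits.** The Discussion sentence beginning "If this protocol takes too much effort for our patients" is a contingency. It goes on to name only the Six-Minute Walk and Trendelenburg tests as candidates for removal, and TGUG is not among them.
- **That the bias has a known size.** If exactly the worst 15% of one arm were lost and nobody from the other, a normal mean would shift by 0.233/0.85 = 0.27 SD. Nothing in the article supports that pattern; it is an extreme case, not an estimate.
- **That a mixed model cures everything.** Values missing because the unobserved TGUG would have been poor are not missing at random, and the mixed model does not generally remove that bias. Nor does a model with unstructured covariance generally reproduce the ANOVA's F test when data are complete.

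**Conclusion.** The point holds in conditional form, as a cheap improvement rather than a demonstrated error. For each continuous outcome, including the primary TGUG, the named ANOVA covers all subjects only if all three values are present or imputed; otherwise it also discards observed visits. The one-factor within-group ANOVA is subject to the same condition.

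At assumed per-visit missingness of 5% to 15%, the ANOVA would drop about 10% to 28% of patients if visits are missed independently (100% − 90.25% and 100% − 72.25%), or 5% to 15% if the same patients miss both. These figures rest on assumed rates, complete baseline data and no imputation. With no missing values the loss is zero.

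**What to change.** Replace the ANOVA for continuous outcomes with a likelihood-based mixed model for repeated measures:

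- fitted by REML, with arm, visit and their interaction;
- baseline either kept as a time level with a common mean in both arms, or used as a covariate;
- small-sample degrees of freedom;
- unstructured covariance across visits, with a simpler structure named in advance in case it does not fit at small numbers;
- every randomised patient with any observed value analysed in the allocated arm.

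The baseline choice affects the set. Kept as a time level, baseline retains patients who have no follow-up value, though they add little to the arm comparison. Used as a covariate, it leaves them out, and the plan should then say so instead of promising all subjects.

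Report by arm and visit how many patients have no TGUG and how many were unable to perform it. Add a sensitivity analysis that gives the worst rank to those unable, since the main model relies on missing at random.

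If the sponsor prefers to keep the ANOVA, state how missing values are imputed or limit the all-subjects statement to patients with complete data.

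**Cost.** The change needs no new data and slightly more analysis work. The mixed model can be fragile at very small sample sizes, and its results need not match the ANOVA even with complete data. Trial status says recruitment has ended and the trial is at the analysis stage, so the change should be dated and should state whether outcome data had been seen by arm.

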## Discussion

The aim of this study is to assess the difference in functional outcome after THR through the PAA, compared to THR through the AA. The main difference between these two approaches is their impact on the gluteus medius. Whereas the AA detaches two thirds of the gluteus medius, the PAA only detaches a small part of the muscle. Since the gluteus medius is one of the most important muscles for the stability of the hip joint [10–12], we hypothesize that functional outcome is better or is achieved faster if THR surgery is performed through the PAA instead of the AA.

For this study we chose to have multiple outcome measures (SEMG, strength of gluteus medius and quadriceps, the Trendelenburg test score, the 6MWD and scores on the OHS, SF-36, TGUG and 5tSTS tests) to be certain we measure all possible effects. According to Vissers *et al*. three aspects should measure functional outcome: self-perceived function, functional tests in a laboratory setting and actual daily activity [4]. Both self-perceived function (measured by the OHS and SF-36 questionnaires) and functional tests (measured by the 6MWT and the TGUG, 5tSTS and tests) are use as outcome measures in our study. However, we chose not to assess actual daily activity at this stage. Rasch *et al*. reported remaining muscle atrophy up to two years after THR [5]. Therefore, we chose to include muscle strength measurements (measured by the SEMG, MicroFET and Trendelenburg tests). If this protocol takes too much effort for our patients it is possible that we could reduce it by removing the 6MWT and the Trendelenburg test.

This study has the following limitations. First, complete blinding cannot be achieved because of the SEMG measurements of the gluteus medius and the difference in location of scar tissue for both surgical approaches. Therefore, we chose to have an independent researcher carry out SEMG measurements and note the results, ensuring the other measures will be blinded. Second, we will only evaluate the short-term outcome. Because of the difference in approach we assume that the intervention group will already show a great deal of improvement in the short-term, while the control group will improve less. In later studies it will be necessary to investigate long-term success as well.

The following strengths can be mentioned. First, we conduct a single centre study, ensuring a standardized approach. Second, we use a wide range of outcome measures allowing us to achieve a total picture of the rehabilitation process. This is why patients are asked to complete both a generic (SF-36) and a disease-specific questionnaire (OHS). The disease-specific questionnaire is believed to better measure changes in function. The generic questionnaire is used to detect changes in psychosocial terms as well.

## Trial status

Statistical analysis. Recruitement began October 2013 and was finished in September 2014.

## Abbreviations

1RM: One repetition maximum
5tSTS: Five times Sit-to-Stand
6MWD: Six-minute walking distance
6MWT: Six-Minute Walk test
AA: Anterolateral approach
ANOVA: Analysis of Variance
BP: Bodily Pain
CVA: Cerebrovascular accident
HRQol: Health-related quality of life
MVIC: Maximal voluntary isometric contraction
OHS: Oxford Hip Score
PAA: Percutaneous assisted approach
PF: Physical functioning
RP: Role physical
SEMG: Surface-electromyography
SF-36: 36-item Short Form Health Survey
SLS: Single leg stance
TGUG: Timed Get-Up-and-Go
THR: Total hip replacement
UC: Usual care
UZA: Universitair Ziekenhuis Antwerpen (Antwerp University Hospital Antwerp)
ZNA: Ziekenhuis Netwerk Antwerpen (Hospital Network Antwerp).
